## Background

Type 2 diabetes (T2D) is a chronic and increasingly common disease linked to changes associated with sedentary lifestyles and inappropriate food energy intake [1]. The prevalence of known and treated diabetes is close to 4% in France, and up to 18% among adults aged over 30 years in Reunion Island, a French overseas region [2]. This situation gives rise to major costs, with overall expenditure in France estimated at €5,710 billion in 2000 [3]. In Reunion, the financial direct impact associated with diabetes and its complications is estimated at €5,451 per patient [4].

Intervention trials in T2D have clearly shown that complications can be prevented or delayed by rigorous control of the blood sugar level and risk factors [5,6]. An improvement of one point in HbA1c is associated with a 20% decrease in the occurrence of macrovascular complications and 30% to 40% decrease of microvascular complications [6]. Diabetes and the associated risk factors nevertheless remain poorly controlled for the most part [7,8]. In Reunion Island, as in France, glycaemic targets are not achieved: in the REDIA study, HbA1c was 8.4 ± 0.2% in patients treated with oral antidiabetic drugs (OAD) and 9 ± 0.5% in insulin-treated patients [2].

For subjects with T2D, four imperatives must be maintained over the long term to contribute to the prevention of complications: adherence to diet, physical activity, treatments and monitoring checks. In order to achieve these objectives the treatment, and optimum medical follow-up, must be associated with therapeutic patient education [9-11]. Self-management education (SME) aims to help patients to acquire or maintain the skills they need to manage their life with a chronic disease as effectively as possible [12]. These education actions must be based on solid theoretical foundations which take into account the complexity of the chronic disease [13-16] and the integration of the individual [15,17,18] in his or her social, family and cultural environment, as part of an appropriate approach taking into account social configurations [19,20] and capacities for change [21].

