### Eligibility criteria

1. Inclusion criteria: patients aged over 18 with type 2 diabetes, defined in accordance with WHO criteria treated for at least one year (OAD and/or insulin and/or GLP-1 analog); HbA1c ≥ 7.5% for three months or over; treatment regimen stable for at least three months (except for possible changes to insulin doses in the previous three months); living in Reunion Island, affiliated to French national health insurance, and patients having signed a consent form for participation in the trial.

2. Non-inclusion criteria: current or scheduled treatment liable to influence blood sugar levels, such as corticotherapy; current or recent hospitalisation (< three months) associated with the diabetes; structured education intervention in hospital or on outpatient basis in previous three months; severe evolving current complication: ischemic or proliferative retinopathy, severe chronic renal insufficiency (clearance < 15 ml/min), coronary heart disease, foot lesions; current pregnancy or desire for pregnancy during the trial; evolving cancer (except baso-cellular or spino-cellular cutaneous epithelioma); severe physical, cognitive or mental illness handicap; concomitant participation in a therapeutic intervention trial.

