### Outcomes

The main outcome is the evolution of HbA1c (%) at two years. The HbA1c will be measured by the HPLC method in a centralised laboratory (biochemistry laboratory of the Félix Guyon hospital in St Denis).

The secondary outcomes will be as follows: quarterly evolution of HbA1c (%), fasting blood glucose, anthropometric indicators (body mass index, waist circumference), blood pressure, tobacco consumption, annual screening of lipids (total cholesterol, triglycerides, HDL and LDL cholesterol), antidiabetic treatments (type and dose) and the occurrence or worsening of diabetic complications. Health practices (level of physical activity and food consumption) will be assessed by means of annual questionnaires. These have been used in Reunion Island for a number of descriptive or intervention studies: RECONSAL [50], REDIA-prev1 [51] and REDIA-prev2 [31]:

Physical activity: physical activity scores will be assessed by means of a questionnaire developed on the basis of the Baecke self-questionnaire [52], which explores professional, sporting and leisure exercise. Questions on domestic activity were added to our studies.

Food consumption: food consumption (reported energy intake, macronutrient intake, dietary habits) will be assessed by means of a rapid food frequency questionnaire relating to weekly consumption [53]. Quantities of various foods are assessed by means of a photo album. The validity of the questionnaire and the photo album for the population of Reunion was checked by comparison with food surveys.

The care and treatment courses will be assessed by means of questionnaires at inclusion and at two years, based on the questionnaire used in the French ENTRED study [54] adapted to the situation and context in Reunion and comprising 30 items.

Quality of life will be assessed annually by means of the Diabetes Quality of Life, Brief Clinical Inventory [55]. This scale, including 15 items and translated into French for Reunion, was validated for this trial among a sample of 150 Reunion’s patients presenting diabetes.

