### Sample size consideration

The efficacy assessment is based on the following main judgement criterion: developments between inclusion (week 0) and two years (week 96) of the percentage of glycated haemoglobin HbA1c (%).

The expected benefit is a decrease at two years of at least 1% in the average HbA1c between the group “structured on-going SME support” and the control group “Initial structured education cycle only”. An absolute difference of 1% at two years between the two groups appears relevant [23,24,29,32,39,60-62].

To show an absolute difference of 1% of HbA1c, with a standard deviation of 2.5%, a type I error rate of 5% and a power of 80%, it is necessary to include 99 subjects per group in a bilateral situation.

Because of an estimated data deficiency of 20% at two years (drop out, refusals, deaths), it is planned to include 120 subjects per group, making a total of 240.

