### Statistical methods

The statistical analyses will be carried out at the CIC-EC in Reunion, under SAS® (version 9.2, SAS Institute Inc., Cary, NC, USA).

Description of the initial characteristics of the screened patients and of the included patients will be done by usual statistics (number, percentage, average ± standard deviation or median and range).

Effective implementation of the SME program and the effective participation will be documented.

The assessment of efficacy of the intervention will be performed in a single analysis, according to the intention to treat principles (*i.e.* according to group allocated by randomisation) with type I error equal 5%, and bilateral formulation of Student t-test (primary analysis).

In the two compared groups, the deficient data on HbA1c (%) at two years (week 96) will be replaced by the measurement obtained at week 84.

If the primary analysis shows a significant difference between the two groups, a comparison of the mean change in HbA1c (%) S96-S0 will be done by the level of participation (secondary analysis using 1-factor ANOVA model): i) basic level ("initial structured therapeutic education only"), ii) level 1 (“structured on-going SME support” without specific additional focused sessions), iii) level 2 (“structured on-going SME support” with specific additional focused sessions).

Analysis of longitudinal data gathered during two years will used in generalised estimating equations (GEE) adapted to repeated measurements in order to test the trends described over the duration of the supervision.

Analysis of the time between randomisation and occurrence of a level of HbA1c <7% (first event observed) will be performed by the Kaplan-Meier method, with comparison of survival curves between groups by Log-rank test.

At each annual collection point the anti-diabetic treatments will be classified into four hierarchical categories: 1) non-insulin antidiabetic monotherapy, 2) non-insulin antidiabetic bi-, tri- (or more) therapy, 3) one injection of insulin, 4) two or more injections of insulin. Between two collection points, moves from one category to a higher (or lower) category will be identified as a reinforcement (or reduction) of the treatment. The interaction between the intervention and treatment category will be tested in the appropriate multivariate models (ANCOVA, GEE, time-dependent variable in the Cox model).

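### The comparison of time to HbA1c below 7% leaves out week-0 HbA1c: the log-rank test is valid, but baseline adjustment could add about 0 to 8 points of power

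*Protocol article*

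**What the plan says.** Under Statistical methods, the time from randomisation to the first observed HbA1c below 7% is analysed by Kaplan-Meier, "with comparison of survival curves between groups by Log-rank test". No covariate or stratum is attached to that test. A Cox model appears later in the same section, but only among the models for testing an interaction between intervention and drug-treatment category. Baseline HbA1c is not mentioned there.

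Three other sections bear on the point:

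- **Eligibility criteria** require "HbA1c ≥ 7.5% for three months or over" and state no upper limit.
- **Randomisation methods** stratify on insulin use and centre, not on HbA1c.
- **Sample size consideration** defines the main criterion as "developments between inclusion (week 0) and two years (week 96) of the percentage of glycated haemoglobin HbA1c", so a week-0 value is needed for every patient. Outcomes adds "quarterly evolution of HbA1c" as a secondary measure.

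The primary analysis is a t-test. The document states no event rate, hazard ratio or power for the time-to-event comparison.

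**The concern.** The event is the baseline variable itself crossing a fixed line. Two patients with the same response to education can differ in whether and when they have the event only because one started closer to 7%. If later HbA1c is positively correlated with week-0 HbA1c, the starting value predicts the event, and an arm comparison that leaves it out gives up some power. Insulin use and centre need not stand in for it.

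Starting HbA1c is also not balanced by design, so the arms may differ in it by chance. The log-rank test allows for this on average over repeated trials, but it cannot correct for the imbalance in the trial actually run.

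What is at stake is efficiency in a secondary analysis, not the validity of the trial.

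**Working it through.** **Plan's own figure.** The only sample-size figure concerns the primary outcome: "To show an absolute difference of 1% of HbA1c" "with a standard deviation of 2.5" points, two-sided 5%, 80% power. n per arm = 2 × (1.960 + 0.842)² × 2.5² / 1² = 98.1, so 99, as stated. Nothing comparable exists for the time-to-event endpoint.

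**Distance to the event.** A patient entering at 7.5% must fall by more than 7.5 − 7 = 0.5 points; one entering at 10% by more than 10 − 7 = 3 points.

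**Chance imbalance (baseline SD assumed, 1.15 to 1.7).** The SE of the between-arm difference is SD × √(2/120), or 0.15 to 0.22. The 95% range is therefore about ±0.3 to ±0.4 points, against a target effect of 1 point.

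**Simulation A (assumptions not in the document).** 240 patients; baseline at least 7.5 with SD 1.7 before truncation; quarterly visits; 20% random loss; 400 trials per scenario. Log-rank was compared with Cox adjusted for week-0 HbA1c.

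- Week 0 to 96 correlation about 0.42, 1-point linear divergence: power 61% vs 68%.
- Same correlation, 0.7-point divergence from week 24: 81% vs 88%; hazard ratio 1.91 vs 2.10.
- Same correlation, 0.7-point linear divergence: 30% vs 33%.
- Correlation 0.25: gain of about 1 point.
- No effect: rejection rates 4.0% and 5.5%.

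**Simulation B (also assumed).** 120 per arm; baseline normal (8.8, SD 1.5) truncated at 7.5; visits every 12 weeks to week 96; 20% dropout; arm effect rising linearly from week 12 to 1 point at week 96; 600 trials per scenario. The unadjusted test is a Cox model with arm only, in effect the log-rank test. For context, the Background gives local values: "HbA1c was 8.4 ± 0.2% in patients treated with oral antidiabetic drugs (OAD) and 9 ± 0.5% in insulin-treated patients".

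Truncated baseline SD: a = (7.5 − 8.8)/1.5 = −0.867; λ = φ(a)/(1 − Φ(a)) = 0.274/0.807 = 0.340; SD = 1.5 × √(1 + aλ − λ²) = 1.5 × √(1 − 0.294 − 0.115) = 1.15.

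Implied correlation of baseline with a later value = (slope × 1.15) / √[(slope × 1.15)² + person SD² + visit SD²].

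| Slope | Person SD, visit SD | Correlation | SD of change | Power, unadjusted | Power, adjusted | Hazard ratio, unadjusted to adjusted |
|---|---|---|---|---|---|---|
| 0.3 | 1.2, 0.5 | 0.345/1.345 = 0.26 | 1.5 | 66.2% | 66.2% | 1.96 to 1.98 |
| 0.6 | 2.0, 0.8 | 0.69/2.262 = 0.31 | 2.2 | 24.5% | 25.8% | 1.30 to 1.30 |
| 0.6 | 1.0, 0.5 | 0.69/1.314 = 0.53 | 1.2 | 75.2% | 76.5% | 2.07 to 2.14 |
| 0.9 | 0.8, 0.4 | 1.035/1.368 = 0.76 | 0.9 | 74.8% | 83.0% | 2.15 to 2.35 |

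The gains are 0, 1.3, 1.3 and 8.2 points. With a 0.5-point effect, in the same row order, power goes from 17.2% to 17.5%, 8.3% to 9.5%, 19.8% to 20.7% and 22.0% to 25.5%. With no effect, rejection is 3.8 to 5.5% unadjusted and 2.8 to 5.7% adjusted. The standard error of one power figure near 75% is √(0.75 × 0.25/600) = 1.8 points; the paired differences are more precise.

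**Reading the two together.** Adjusted power was never below unadjusted power. With weak tracking (correlation 0.25 to 0.31) the gain is 0 to about 1 point. With moderate or strong tracking (0.42 to 0.76) it lies between about 1 and 8 points, depending on the effect pattern and the tracking.

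**The case against.** The strongest reply is that nothing here is an error. Kaplan-Meier with a log-rank test is a standard pairing, it holds its 5% level under randomisation, and the article is a condensed document whose unseen analysis plan may add covariates. The analysis is secondary and carries no power claim. All of that stands, which is why this is an efficiency suggestion. What remains is that the article does name the test, and a better use of data already collected is available.

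Three stronger readings are tempting, and the document supports none of them:

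- **That starting HbA1c is the main determinant of reaching 7%.** This is an inference from the event definition. The protocol gives no baseline-to-follow-up correlation.
- **That the unadjusted analysis biases or dilutes the effect.** The unadjusted hazard ratio is marginal and the adjusted one conditional. They answer different questions, and the plan announces no hazard ratio for this endpoint.
- **That the planning SD of 2.5 shows a wide spread of starting values.** It belongs to the primary outcome at two years. If anything it points the other way, because a large SD of change unrelated to baseline makes starting HbA1c less decisive. The scenario nearest to it (SD of change 2.2) gains about 1 point.

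Adjustment also has a price. The Cox model assumes a functional form for baseline HbA1c and proportional hazards. Both arms receive the same education until week 12, so the hazards may coincide early and separate later. A single hazard ratio would then average over a changing effect.

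**Conclusion.** The point holds as a low-severity improvement. The planned log-rank test is valid, but it leaves out a baseline value that is already collected and that fixes each patient's distance from the event. The cost is about 0 to 8 percentage points of power. It is negligible if later HbA1c follows baseline weakly and reaches 7 or 8 points only in some scenarios with moderate or close tracking. These sizes rest on an assumed baseline distribution, correlation and effect pattern, none of which the document gives. Type I error is essentially the same either way, and the primary conclusion does not depend on this analysis.

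**What to change.** Prespecify the arm comparison for time to HbA1c below 7% as a Cox model with arm and continuous week-0 HbA1c, reporting the adjusted hazard ratio with its 95% CI. Keep the Kaplan-Meier curves and the unadjusted log-rank test as supportive. State how the linear term for baseline HbA1c and the proportional-hazards assumption will be checked, with attention to the common period up to week 12.

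A log-rank test stratified by week-0 HbA1c category is an alternative that needs no linear term. In simulation B, a Cox model stratified by baseline tertile had power of 66.0%, 24.8%, 75.0% and 82.8% in the table's row order. It therefore kept the gain where tracking was close and changed almost nothing elsewhere.

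The cost is a sentence or two of analysis wording and no new data. Fixing it before outcomes are seen also avoids a post hoc choice should starting HbA1c turn out unequal between the arms.

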### Concomitant treatments and procedures

In both arms, patients will continue to receive quarterly outpatient medical follow-up. Regular examinations and therapeutic adaptation will take place in accordance with the recommendations. The individual nursing or dietician encounters, required in addition to the medical appointments due to the evolution of the disease or therapeutic changes (such as starting insulin, GLP-1 analogue) will be authorised whatever the arm.

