## Discussion

Available studies which were carried out on the basis of these inclusion criteria (adult diabetes patients remaining at very high risk of complications due to persistent poor blood glucose control with HbA1c in excess of 7.5%) have shown a favourable effect from educational intervention at six months and one year, but the question of the efficacy of maintenance at two years, and of intensification by means of on-going structured intervention at the proximity level, still remains unanswered as compared to a sole initial structured education.

The relatively heterogeneousness of these patients showing insufficient therapeutic control (treatment by OADs or GLP-1 analogue, basal or multi-day insulin therapy) may give rise to significant differences in metabolic control. Randomisation with stratification into two groups in accordance with the addition of insulin therapy will make it possible to balance the spread of treatments between the two arms at the time of inclusion, and to assess situations presenting comparable initial medication treatments. On the other hand, anti-diabetic treatments may mask the effects of therapeutic education on the level of blood glucose control: i.e. the drug therapy reinforcement required due to the lower efficacy of the education in one group could minimise the difference between the two intervention groups. Although that is not the case in the available studies that have assessed this issue, it appears important to record the changes of anti-diabetic treatments occurring throughout the study [22,23,39].

Maintained structured educational on-going support over two years requires co-ordination, in parallel with medical and diabetological supervision, thanks to the existence of an education coordination network in Reunion. The network has the resources and already conducts structured education cycles. Self management education sessions are carried out by trained and experienced health care professionals, with an empowerment approach. The SME style is theoretically based and reproducible, with curricula and handouts making it possible to renew educational actions on the same bases. The potential investment of peer educators or expert patients has not been retained for this ERMIES study design, since the French and Reunion context is currently not yet ready to include such issues. However, this is an important clue to evaluate and implement in the future [37-39].

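### Antidiabetic treatment is classified only once a year, yet the category feeds secondary GEE and time-dependent Cox analyses of data that move quarterly

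*Protocol article*

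**What the plan says.** All references are to the protocol article.

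- **Statistical methods, timing:** "At each annual collection point the anti-diabetic treatments will be classified into four hierarchical categories". The four categories run from non-insulin monotherapy up to two or more insulin injections.
- **Statistical methods, definition of change:** "Between two collection points, moves from one category to a higher (or lower) category will be identified as a reinforcement (or reduction) of the treatment".
- **Statistical methods, use:** the interaction of intervention and treatment category "will be tested in the appropriate multivariate models (ANCOVA, GEE, time-dependent variable in the Cox model").
- **Concomitant treatments and procedures:** "In both arms, patients will continue to receive quarterly outpatient medical follow-up", and "Regular examinations and therapeutic adaptation will take place in accordance with the recommendations".
- **Outcomes:** the first secondary outcome listed is "quarterly evolution of HbA1c". Antidiabetic treatment (type and dose) is also a secondary outcome, but it stands in a list that mixes quarterly and annual items, so its collection frequency is not clear.
- **Discussion:** drug reinforcement in the arm where education works less well could shrink the difference between arms. The available studies that looked did not find this, but "it appears important to record the changes of anti-diabetic treatments occurring throughout the study".

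No section gives a classification more frequent than annual.

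**The concern.** The treatment category is the plan's instrument for examining whether drug changes blur the effect of education. Both the treatment and the HbA1c can change every quarter, but the category is refreshed only once a year. A covariate in a repeated-measures model, and above all one labelled time-dependent in a Cox model, should describe the patient's state when the outcome is observed. Under the stated rule it mostly describes an earlier state.

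Two things suffer. Within a year, the order of a drug change and an HbA1c change cannot be recovered from the category. A step up followed by a step down between two annual points also counts as no change. At stake is the reading of the secondary treatment-interaction analyses.

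**Working it through.** The document gives no figure for the timing of the classification, so there is nothing of its own to reproduce here. The check counts visits.

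**Inputs**
- Follow-up runs from week 0 to week 96 (Sample size consideration).
- Visits are 12 weeks apart. This is inferred from quarterly follow-up and from week 84 being the substitute for a missing week-96 value (Statistical methods).
- Post-baseline HbA1c values: 96 / 12 = 8.
- Annual points at weeks 0, 48 and 96. Week 48 is an assumption; the article does not state it.
- The last category is carried forward between annual points. This too is an assumption; the article gives no alignment rule.
- The Cox model is read as a model of time to HbA1c below 7%, the only time-to-event analysis described.

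**Age of the category at each HbA1c value** (HbA1c week minus week of last classification)

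| HbA1c week | Last classified | Age (weeks) |
|---|---|---|
| 12 | 0 | 12 |
| 24 | 0 | 24 |
| 36 | 0 | 36 |
| 48 | 48 | 0 |
| 60 | 48 | 12 |
| 72 | 48 | 24 |
| 84 | 48 | 36 |
| 96 | 96 | 0 |

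The category is concurrent at 2 of 8 values and 12 to 36 weeks old at 6 of 8.

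**Cox covariate.** It starts at the week-0 category and is updated at week 48. The week-96 value arrives as follow-up ends, which leaves one usable update. A first HbA1c below 7% at week 12, 24 or 36 is analysed under the inclusion category. Filling back from week 48 instead would use information from after the event.

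**Delay until a lasting move is seen.** This depends on when changes take effect:
- Already in force at a visit (weeks 12 to 96): 36, 24, 12, 0, 36, 24, 12, 0. The mean is 144 / 8 = 18 weeks and the maximum 36.
- Spread evenly over time: the mean is 48 / 2 = 24 weeks.
- Just after a visit (weeks 0 to 84): 48, 36, 24, 12, 48, 36, 24, 12. The mean is 240 / 8 = 30 weeks and the maximum 48.

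With quarterly classification the corresponding means are 0, 12 / 2 = 6, and 12 weeks.

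**Reversed moves.** Take a step up in force at one of the 8 visits and reversed at a later one. There are 8 × 7 / 2 = 28 such pairs. A pair is invisible when both visits fall in weeks 12 to 48 (4 × 3 / 2 = 6) or both in weeks 60 to 96 (6). That gives 12 / 28 = 43% of patterns. This is a share of possible patterns, not of patients; the article gives no frequency of moves.

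**Example.** A patient moves up a category at week 12, has HbA1c below 7% at week 24, and moves back down at week 36. The categories at weeks 0 and 48 are equal, so the rule counts no reinforcement. With carry-forward, the week-24 event falls under the inclusion category.

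**The case against.** The strongest reply is that classifying is not recording. A reader might infer that the trial records treatment only once a year and so loses interim changes. The article does not support that. The Outcomes section leaves the frequency for treatment type and dose open, and the Discussion wants changes recorded throughout, so dated data may well exist. This stands, and it limits the point to the analysis rule. It does not remove the point, because an annual category would leave such data unused in the GEE and Cox models.

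Carry-forward and week 48 are assumptions, and covariate coding is often left to an analysis plan. That also stands for the exact ages in the table. But the annual timing is a stated rule, not a gap. With one category a year, no alignment rule makes it current at the other quarterly values.

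The definition of a move could be read as catching changes inside the interval. Since categories exist only at the annual points, comparing consecutive points is the natural reading.

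A reader might also infer that the trial could not tell whether a null result was masked by drugs. That goes too far. The primary comparison runs from week 0 to week 96, and the annual categories would still show by arm whether patients ended on a higher category than they began. In the example above, the patient is back in the inclusion category 60 weeks before the endpoint (96 − 36 = 60). Nor does the Discussion call masking the main threat; it is raised as a possibility not seen in earlier studies.

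**Conclusion.** The point holds as a mismatch between the annual classification and the secondary models that use it. On the assumed schedule (weeks 0, 48, 96; 12-week visits), the category is current for 2 of 8 post-baseline HbA1c values. With carry-forward it is 12 to 36 weeks old at the other six, and the time-dependent Cox covariate has a single usable update. Moves reversed within a year disappear from the classification. How many patients this touches cannot be judged from the article.

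The effect is confined to the treatment-interaction analyses by GEE and Cox. The primary t-test does not use the category, and neither does the sample size calculation (99 evaluable, 120 planned per group). Net shifts by arm at weeks 48 and 96 remain visible. A 48-week dating delay should not be read as typical: it is the worst case, for a change made just after an annual point. It is worth correcting, but it does not threaten the main result.

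**What to change.** In Statistical methods, move the classification from annual points to each quarterly visit (weeks 0, 12, 24, ..., 96). Define reinforcement and reduction between consecutive quarterly visits. State that this updated category is the one used in the GEE and as the time-dependent Cox covariate. The change concerns measurement and analysis only; it alters no treatment rule.

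If dated treatment data are already collected, the category can be derived from them and the cost is coding. If not, one treatment entry is added at quarterly visits that already take place. Per patient that means 9 classifications instead of 3 (weeks 0, 48, 96), so 6 more, or at most 240 × 6 = 1,440 over the trial before dropout. The downside is slightly more data entry and coding.
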